#### 2.3.2. Exclusion criteria.

Subjects with a history of hypersensitivity or allergies to the study medication components.Subjects who have a history of unstable angina, myocardial infarction, atherosclerotic ischemic stroke, transient ischemic attack, cerebrovascular disease, coronary artery disease, coronary artery bypass graft, percutaneous coronary intervention, peripheral arterial disease, carotid artery disease (significant carotid artery stenosis), or abdominal aneurysm; any malignant tumor within 5 years before screening; drug or alcohol abuse; gastrointestinal surgery or drug absorption disorders due to gastrointestinal disorders.Subjects with unstable hypertension (systolic blood pressure ≥ 180 mm Hg or diastolic blood pressure, diastolic blood pressure ≥ 110 mm Hg), diabetes (taking diabetes medication or fasting blood glucose > 160 mg/dL), aspartate transaminase or alanine transaminase  ≥ 2 × upper normal limit (UNL), estimated glomerular filtration rate  < 30mL/min or creatinine ≥ 2 × UNL; creatine kinase > 2 × UNL or a history of myopathy or rhabdomyolysis, thyroidal disease, pancreatitis.Subjects who have administered a concomitant drug during the clinical trial or are judged to have unavoidable administration of a concomitant drug.Subjects who used drugs and food that can affect lipid profile within 4 weeks prior to the screening (statins, fibrates, bile acid sequestrants, niacin, anti-obesity drugs, steroids for systemic action, fish oil, omega-3, cholestin products, fiber-based laxatives, and phytosterol margarine, among others).Subjects who participated in other clinical trials within the last 3 months.Female subjects who are pregnant or lactating.Female subjects who plan to conceive.Subjects who the investigator considers to be inappropriate to participate in the trial.

### 2.4. Recruitment

The trial will be conducted at 2 hospitals as follows: Kyung Hee University Oriental Medical Center and Wonkwang University Gwangju Medical Center. Posters will be posted publicly, both inside and outside the hospitals. Investigators will provide research information, including the objectives, procedures, and potential benefits and risks, to participants through standardized interviews before their participation, and informed consent will be obtained from all participants. Participants will be allowed to withdraw from the study at any time without disadvantage and will be immediately notified when new information regarding the study is obtained.

### 2.5. Interventions

Before allocation into groups, all participants will be educated and instructed to follow dietary and exercise guidelines for hyperlipidemia using a brochure based on the Guidelines by the Korean Ministry of Food and Drug Safety for clinical trials for hyperlipidemia treatment for 4 weeks.^[24]^ After 4 weeks of lifestyle modification, eligible participants will be randomly assigned to receive GBH or placebo granules for 8 weeks. GBH, a light brown granular substance, will be prepared by Hanpoong Pharm and Foods Co., Ltd. (Batch number: 20001; Wanju, Jeollabuk-do, South Korea). It will be produced according to the Korean Good Manufacturing Practice guidelines outlined by Korea Ministry of Food and Drug Safety and manufactured so that there is no difference between them in shape, color, smell, or taste. A blinded pharmacist will check the storage, dispensation, and quality of the investigational products. GBH is made of an extract comprising the following herbs: *Cinnamomum cassia* Blume (1.33 g), *Poria cocos* Wolf (1.33 g), *Paeonia suffruticosa* Andrews (1.33 g), *Prunus persica* Batsch, and *Paeonia lactiflora Pallas* (1.33 g), which were extracted with 8 to 10 times the volume of water at 80°C to 100°C for 2 to 3 hours. The extract was filtered, and the filtrate was concentrated under reduced pressure at 60°C or lower to obtain the herbal extract. The placebo granule was made of corn starch, lactose hydrate, hydroxypropyl methylcellulose, Opadry® 200, and caramel coloring.

Participants will be instructed to take 1 pack (4.0 g) 3 times daily for 8 weeks. The dosage regimen is based on an authorization from the Korean Ministry of Food and Drug Safety. Participants will be instructed to return unopened packages of the investigational product to check their adherence to the treatment. If any adverse events occur, investigators will take appropriate action depending on the severity of the adverse event and its causal relationship with the investigational product.

Co-administration of medications used for managing metabolic diseases, such as hypertension and diabetes, and dietary supplements that do not directly affect hyperlipidemia can be permitted during the study period. However, participants will be instructed not to change the dose or type of concomitant medication as much as possible, if they are changed, and the investigators will record the details in the case report form (CRF).

The use of fibrates, bile acid sequestrants, niacin, anti-obesity drugs, steroids intended for systemic action, fish oil, colestine products, fiber-based laxatives, phytosterol margarine, which can affect the lipid profile, the drugs usage that can affect thyroid function, such as thyroxine, and will be prohibited during the study period.

### 2.6. Outcomes measures

#### 2.6.1. Primary outcome.

Percentage changes in LDL-C from the baseline to week 8.

#### 2.6.2. Secondary outcomes.

Percentage changes in TC, HDL-C, TG, apolipoprotein A1, and apolipoprotein B from the baseline to week 8.Other blood lipid parameters.Changes in the total scores of blood stasis questionnaire.

#### 2.6.3. Exploratory outcomes.

As an exploratory outcome measure, metabolite analysis will be conducted to observe the changes in metabolic patterns.

### 2.7. Safety and adverse events

The safety of the investigational product will be measured by comparing the laboratory liver and renal function test results (aspartate transaminase, alanine transaminase, gamma- glutamyl transferase, blood urea nitrogen, and creatinine) before and after the intervention in each group. Investigators will also examine the adverse events at each visit, which will be recorded in this study. Additionally, and investigators will ensure that all participants with adverse reactions receive adequate medical attention and follow-up until symptoms are resolved.

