**Discussion::**

This is the first randomized controlled trial to explore the clinical effect and safety of GBH compared to placebo control in patients with hyperlipidemia, thereby potentially facilitating better management of hyperlipidemia. The results of this pilot study could form a foundation for future large-scale confirmatory clinical trials.

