In traditional East Asian medicine, hyperlipidemia is regarded as the retention of phlegm and fluid disease, having similar etiology and pathogenesis based on spleen-deficiency and phlegm-stagnation, accumulation and stasis of heat, and qi and blood stagnation induced by phlegm-damp, water-dampness, and blood stasis. Therefore, strengthening the spleen, dissolving phlegm, clearing away heat and diuresis, supplementing qi, and activating blood circulation are commonly used therapeutic methods for hyperlipidemia.^[9–13]^

In Korea, (Gyejibongnyeong-Hwan [GBH]; Gui Zhi Fu Ling Wan in traditional Chinese; and Keishibukuryogan in Kampo medicine) is an herbal medicine comprising 5 herbs, including *Cinnamomum cassia* Blume, *Poria cocos* Wolf, *Paeonia suffruticosa* Andrews, *Prunus persica* Batsch, and *Paeonia lactiflora* Pallas, widely used to treat several symptoms of blood stasis, which collectively refers to pathological conditions of blood circulation disorder in clinics.^[14,15]^ It has been reported to have antilipid, antiplatelet, antithrombotic, and antiatherosclerosis.^[14]^ In particular, a significant number of preclinical and clinical studies have been reported that have identified the blood lipid-lowering effects of GBH.^[14]^

However, few clinical studies have evaluated the effects of GBH in patients with dyslipidemia in Korea. In other studies, the target lipid parameters of GBH, such as total cholesterol (TC), TG, and LDL-C, have been reported differently according to clinical studies.^[16–21]^

Therefore, this study aims to evaluate the clinical effect and safety of GBH on serum lipid levels and CV risk in patients with borderline hyperlipidemia.

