## 2. Methods

### 2.1. Study design and setting

This is a study protocol for multi-center, randomized, double-blind, placebo-controlled, parallel, investigator-initiated pilot study. Subjects will be recruited from 2 hospitals, Kyung Hee University Oriental Medical Center (Seoul) and Wonkwang University, Gwangju Medical Center (Gwangju), between November 2021 and December 2022. The study period will include 4 weeks of lifestyle modification, 8 weeks of medication, and 4 weeks of follow-up. The study period procedure is summarized in the Consolidated Standards of Reporting Trials (CONSORT) diagram (Fig. 1), and the schedule of enrollment, intervention, and assessments is summarized in Table 1. The trial will be performed in accordance with the Declaration of Helsinki and the Good Clinical Practice Guidelines. This study was sponsored and managed by the Korea Institute of Oriental Medicine (KIOM) during the study period. KIOM wrote the protocol following the CONSORT Extension for Chinese Herbal Medicine Formulas 2017^[22]^ and Standard Protocol Items: Recommendations for Interventional Trials 2013 statement.^[23]^

**Table 1 T1:** Schedule of enrollment, interventions, and assessments.

	Study period					
	Screening		Post allocation			Follow-up
Time point	1st (−4 w)	2nd (±7 d)	Baseline (−14 d)	W 4 (±7 d)	W 8 (±7 d)	W 12 (±7 d)
Enrollment						
Informed consent	●					
Eligibility screen	●					
Demographic characteristics	●					
Medical history	●					
Random allocation			●			
Interventions						
Dietary and exercise education	●	●	●	●	●	
GBH or placebo			← - - - - - - - - - - - - - - - - - - - - →			
Assessments						
Vital sign	●	●	●	●	●	●
Laboratory testing*	●	●		●	●	●
Pregnancy testing		●		●		
Blood stasis questionnaire	●		●		●	
Blinding test					●	
Adverse events			●	●	●	●
Medication compliance				●	●	

GBH = Gyejibongnyeong-Hwan.

* Including hematological test, blood lipid parameters, blood glucose parameter, liver and renal function test, and urine test.

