## 4. Discussion

This is a study protocol for a randomized, double-blind, placebo-controlled, parallel, investigator-initiated pilot clinical trial evaluating the effect of GBH on patients with borderline hyperlipidemia. We will evaluate the preliminary efficacy and safety of an 8-week administration of GBH compared with placebo granules and assess the feasibility of large-scale randomized controlled trials (RCTs). To the best of our knowledge, this is the first RCT to assess the effect of GBH in patients with hyperlipidemia.

GBH is 1 of the most frequently prescribed herbal medicines for patients with impaired blood circulation, known as blood stasis syndrome in Korea, China and Japan.^[27]^ The main components of GBH, such as amygdalin derived from *Persicae Semen*, paeoniflorin derived from *Paeoniae Radix*, and cinnamic acid derived from *Cinnamomi ramulas*, have antilipid, antiplatelet, antithrombosis, and antiarteriosclerosis effects.^[14]^

GBH is not approved by the ministry of food and drug safety as a medicine for dyslipidemia^[15]^ but a significant number of preclinical and clinical studies have been reported that have identified the blood lipid-lowering effects of GBH.^[16–21]^

If the treatment effect and safety of GBH compared to placebo granules are found to be promising in this study and the study design is feasible, we will design a confirmatory, large-scale RCT based on the results of the study to draw definitive conclusions regarding the efficacy of GBH.

In conclusion, this article presents a protocol for a rigorously well-designed, double-blind, placebo-controlled pilot RCT of GBH in patients with hyperlipidemia. The strengths of our study include using placebo granules as the control and using the objective blood lipid parameter, LDL-C, as the primary outcome to minimize performance bias and detection bias. The findings of this study are expected to provide a basis for large-scale, confirmatory RCT to confirm the efficacy and safety of GBH in treating patients with hyperlipidemia. Additionally, stronger evidence for GBH as a treatment option for hyperlipidemia may be provided to clinicians, patients, and researchers.

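### Section 2.7 sets laboratory safety as a before-versus-after comparison within each arm, which does not answer the stated aim of safety compared with placebo

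*Protocol article*

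**What the plan says.** **The aim is comparative.** The Discussion part of the Abstract presents the trial as the first of its kind "to explore the clinical effect and safety of GBH compared to placebo control in patients with hyperlipidemia". Section 4 says "We will evaluate the preliminary efficacy and safety of an 8-week administration of GBH compared with placebo granules".

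**The laboratory safety comparison is within arm.** Section 2.7 compares five liver and renal tests: AST, ALT, GGT, "blood urea nitrogen, and creatinine) before and after the intervention in each group". On adverse events it adds: "Investigators will also examine the adverse events at each visit, which will be recorded in this study". It states no comparison between arms for either kind of data.

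**Section 2.12** has one sentence on safety, which defines who is analysed: everyone who took at least one dose. Independent-sample tests (t or rank-sum, chi-square or Fisher) appear in the paragraph that summarises participant characteristics. Paired tests are assigned to within-group changes in outcome measures. Neither family is tied to safety by name.

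**Table 1** schedules laboratory tests at both screening visits and at weeks 4, 8 and 12. Its footnote gives a wider panel than Section 2.7 names: "Including hematological test, blood lipid parameters, blood glucose parameter, liver and renal function test, and urine test".

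**The concern.** A placebo arm is there to show what would have happened to the laboratory values without GBH. A before/after comparison within each arm does not use it. The change in the GBH arm then contains the following as well as any drug effect:

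- the passage of time;
- diet and exercise education, which Table 1 continues through week 8;
- selection at entry, because Section 2.3.2 excludes AST, ALT or creatinine at or above 2 × UNL, so that later values can drift without any drug.

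If the two arms are tested separately, the natural reading is to compare the verdicts: significant on GBH, not significant on placebo. That can turn shared drift into an apparent signal. It can equally pass over a real difference when both arms, or neither, reach significance. The result has a use, because Section 4 makes a confirmatory trial depend partly on safety looking promising.

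**Working it through.** The protocol gives no SD, event rate or power for safety, so there is no figure of its own to reproduce. The check is of the logic, with an illustration.

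**1. What each comparison estimates.** Write the mean change as

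- GBH arm: shared change + drug effect
- placebo arm: shared change

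The before/after result in the GBH arm estimates the sum. Only the difference between arms estimates the drug effect, because time, education and entry selection act on both randomised arms alike and cancel.

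**2. Inputs for the illustration.**

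- From the protocol: 45 per arm and 20% dropout (Section 2.8), so 45 × 0.8 = 36 per arm after dropout; 1:1 allocation (Section 2.9); two-sided 5% (Section 2.12, stated for the primary outcome and borrowed here).
- Assumed: a paired test in each arm, since Section 2.7 names no test; independent arms; normal approximation; no GBH effect, so both arms share the same true change d, in SDs of change, from 0 to 0.5.

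**3. How often exactly one arm is significant.** The power of a within-arm test is

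p = 1 − Φ(1.96 − d√n) + Φ(−1.96 − d√n)

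and the chance that exactly one arm is significant is 2p(1 − p). Example with n = 36 and d = 0.3: d√n = 1.8, p = 0.437, and 2 × 0.437 × 0.563 = 0.492.

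| Shared change d | n = 36: p | exactly one arm | n = 45: p | exactly one arm |
|---|---|---|---|---|
| 0 | 0.050 | 10% | 0.050 | 10% |
| 0.2 SD | 0.224 | 35% | 0.269 | 39% |
| 0.3 SD | 0.437 | 49% | 0.521 | 50% |
| 0.5 SD | 0.851 | 25% | 0.918 | 15% |

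In half of these cases GBH is the significant arm: at n = 36, about 17% of trials at 0.2 SD and 25% at 0.3 SD. A direct test between arms would be significant in 5% at every d.

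**4. What the between-arm comparison can deliver.** For an unadjusted difference in mean change:

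- Detectable difference at 80% power: (1.96 + 0.84) × √(2/n) = 0.66 SD at n = 36 and 0.59 SD at n = 45.
- Power for 0.5 SD: 56% and 66%.
- Half-width of the 95% CI: 1.96 × √(2/n) = 0.46 SD and 0.41 SD.

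Counts are imprecise too. Suppose, purely as an assumption, 4 of 45 against 0 of 45 with some event. The difference is 4/45 = 8.9 points, and the two-sided Fisher p is 2 × C(45,4)/C(90,4) = 2 × 0.0583 ≈ 0.12.

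**The case against.** The best defence is that Section 2.7 describes how safety is measured, while the analysis belongs to Section 2.12, which lists between-group tests and excludes nothing. A fuller protocol or an SAP may apply those tests to safety data, and an article need not list every table. It is also true that the document nowhere says the before/after comparison is the sole safety analysis.

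Part of this stands. Missing detail on safety tables is no finding. But Section 2.7 is not silent: it names a comparison, and the one it names does not fit the aim. The between-group tests sit with participant characteristics, and the closest match in Section 2.12 to the wording of Section 2.7 is the paired tests. Someone following the text would run two separate within-arm analyses.

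Three stronger readings are tempting and are not supported:

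- **That the trial cannot attribute any safety change to GBH.** It is randomised, blinded and placebo-controlled, both arms are tested on one schedule, and adverse events are recorded in both. The contrast can be computed from the planned data.
- **That haematology and urine tests are dropped from safety.** Section 2.7 does not name them, but Table 1 collects them and nothing says they will go unreported. The Introduction does say of GBH: "It has been reported to have antilipid, antiplatelet, antithrombotic, and antiatherosclerosis". It lists these as reported actions, not as safety concerns. The full list of tests is detail that an article may leave to the full protocol or SAP.
- **That individual elevations will be hidden in group means.** Section 2.7 speaks of test results and does not prescribe means. Tables of threshold crossings are likewise detail for the SAP.

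**Conclusion.** The point holds for the stated laboratory analysis: a within-arm before/after comparison does not estimate safety compared with placebo, and Section 2.7 states no other. This is an error in the stated analysis and not in the design or the data.

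The 35% to 50% figures show why separate within-arm tests mislead. They rest on an assumed shared change of 0.2 to 0.3 SD and on paired tests at 5%. At zero change the figure is about 10%, and it falls again once the change is large. The protocol gives nothing from which to say which case applies. That shared drift exists follows from the design only as a possibility; its size is unknown.

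Severity is minor to moderate. The trial is an exploratory pilot with no stated safety hypothesis, and the primary LDL-C result is untouched.

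**What to change.** In Section 2.7, replace the before/after comparison as the main laboratory safety analysis with a comparison between arms. For each test, give the on-treatment value adjusted for the pre-dose value and report the GBH-minus-placebo difference with a 95% CI. State which visit supplies the pre-dose value: Table 1 has no laboratory test at baseline, so the last one before dosing is at the second screening visit. State also which later visit or visits are compared.

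Compare adverse event incidence by arm. Keep the within-group before/after results as descriptive summaries only. Preferably report the haematology and urine tests already collected by arm in the same way.

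The cost is a few extra tables, with no new procedure, visit or participant. At 36 to 45 per arm the intervals will be wide, so the text should present them as estimates and should not read a non-significant difference as evidence of safety.

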### 2.8. Sample size calculation

This is a preliminary exploratory study to assess the clinical effect and safety of GBH on serum lipid levels and CV risk in patients with borderline hyperlipidemia. According to a study that recommended the minimum sample size for the preliminary study,^[25]^ the minimum effect size was assumed to be 0.20, a dropout rate of 20% was considered, and a total of 90 participants (45 in each group) are set as the target sample size.

### 2.9. Randomization and allocation concealment

An independent statistician will generate a random assignment code using the block randomization method with block sizes in SAS® Version 9.4 (SAS Institute Inc., Cary, NC). Participants who satisfy the eligibility criteria will be assigned to the GBH or placebo granule group at the baseline visit (week 0) with a 1:1 allocation ratio. The generated code will be sealed in opaque envelopes and stored in double-locked cabinets. We will maintain allocation concealment throughout the study period by providing participants with identically packaged, consecutively numbered drug containers.

### 2.10. Blinding

The participants, investigators, outcome assessors, pharmacists, study monitors, and data managers will be blinded to which medication will be administered to participants using placebo granules as a control. An independent statistician who generated the random assignment code will provide the random assignment table directly to Hanpoong Pharm & Foods Co., Ltd. (Jeonju, Republic of Korea), and the company will pack and deliver investigational products to the hospital. The placebo granules will have the same formulation and properties as the HHT granules to prevent any bias in the efficacy and safety assessments. Blinding will be maintained until all participants have completed the study unless serious medical emergencies occur to them. When unblinding is necessary, such as in severe medical emergencies, investigators will open a separate emergency code stored in double-locked cabinets. Investigators must document the reasons for the unblinding. To check whether participant blinding is maintained during the study period, investigators will perform a blinding test on participants after 8 weeks of investigational product administration (Visit 5). Investigators will ask the participants which type of drug they think was administrated: “real drug,” “false drug,” or “do not know.” The success of blinding will be evaluated using the new blinding index and a 95% confidence interval.^[26]^

### 2.11. Data and safety monitoring

We will use a web based electronic CRF for data collection and verification. This will be managed by the data management team from the KIOM. The electronic CRF is accessible only to investigators who are directly involved in the clinical trial and receive relevant education. The range of the data values will be set in advance to ensure the data quality. Although data entry will be performed only once by the investigators, data quality will be managed by 2 verification processes for each clinical research associate and data manager. A clinical research associate at KIOM, a supporting institution, will visit the hospital regularly to monitor protocol violations, recruitment rates, document reporting, and adverse events (including severe adverse events) during the study period. The detected items will be adequately resolved through discussions with the investigators. No formal data-monitoring committee will be convened. Currently, there is no planned audit. However, auditing can be conducted to preserve the integrity of the trial by a quality assurance team at the supporting institution, independent of the investigators.

